### Data collection

#### Outcome and patient-related data

Data will be requested from the Ministry of Health’s National Minimum Dataset (NMDS), the National Surgical Site Infection Improvement Surveillance Programme database and the databases of participating hospitals, and stored in a secure password protected directory within the Faculty of Medical and Health Sciences, University of Auckland. The data will be kept for ten years and then permanently deleted.

In NZ, each patient has a unique National Health Index (NHI) number, and each procedure has a specific International Classification of Diseases 10th Revision - Australian Modification (ICD-10-AM) code. The NHI will be used to link data from different sources and then replaced with a unique study identification number, in the interests of confidentiality.

For this study we will collect the following data: age, gender, ethnicity, weight, height, surgical procedure (including primary or re-operation status) and known comorbidities (with emphasis on those associated with risks of infection and failed wound-healing such as diabetes, severe renal disease, obesity and smoking) [11]. Uncontrolled significant differences in rates of these covariates between groups will be statistically accounted for using quantile regression.

Data for our primary outcome, DAOH_90_, will be requested from the NZ Ministry of Health and will include the date of discharge from hospital and the date of further re-admissions to hospital and will also indicate if the patient dies within the 90-day period.

Information on surgical site infection will be collected from the National Surgical Site Infection Improvement Surveillance Programme, which is limited to patients undergoing government-funded hip and knee arthroplasty and cardiac surgery. For these patients, a standard set of data is collected by trained hospital personnel (predominantly infection prevention and control nurses and perioperative nurses); the data are entered into the national database via an Internet portal. Strategies to ensure that all infections are identified include reviewing hospital microbiology records, having the ward teams alert the infection prevention and control team about suspected infections and reviewing the medical records of patients re-admitted to hospital within 90 days of the relevant procedures.

Patients who underwent their initial operation prior to the implementation of the bundle but are still in hospital during the implementation of the bundle will be included in the analysis of baseline data.

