### Statistics and sample size

DAOH_90_ data have a bimodal, left-skewed distribution that does not lend itself to parametric analysis. Data from a previous study of 20,000 general surgery procedures indicate that most patients score highly, so comparing measures of central tendency between groups can exclude the patients who are most likely to realise improved outcomes. Although our preference would be to use permutation testing methods, our five-cluster, five-sequence design only allows for 120 permutations. We consider this too low a number for a precise estimation of the significance of the difference between control and intervention cases. We will thus use a single Wilcoxon-Mann-Whitney *U* (WMWU) rank sum test as our omnibus test to ascertain whether intervention patients have significantly higher DAOH_90_ than control patients. This WMWU test will also be sensitive to prevailing trends in patient outcomes, so we will further investigate the difference using quantile regression. Models will be fitted at quantiles 0.1, 0.25, 0.5 and 0.75, with DAOH_90_ as the outcome, and time, intervention and site as the predictors. We will characterise any differences in distribution between groups by reporting differences associated with the intervention term in each model, and their significance.

We have used simulations to estimate our statistical power. Datasets were synthesised using distributions generated from four of our sites (excluding Starship Children’s Hospital) with different step lengths. Starship Children’s Hospital data were synthesised on the basis of the distribution from Auckland City Hospital’s cardiac unit. Distributions for each site were tweaked by increasing or decreasing the relative likelihood of higher DAOH scores until the desired magnitude of difference appeared at quantile 0.25. We found that a step length of 180 days (i.e. 6 months) would give us 100% power to detect a 2 DAOH difference at quantile 0.25 between groups using the WMWU and 77.7% power to detect an intervention effect using quantile regression (both two-tailed α < 0.05), with just over 10,000 patients. The intracluster correlation coefficient was measured as 0.02. Cluster sizes in the simulation depended on the ratio of caseloads between sites (see Table 2). Our study statistician has estimated that we will recruit 5492 cases in each group and will require 8454 filter units.

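### Patient covariates enter the quantile regression on a significant group difference, not because they predict DAOH90, so the adjusted model depends on the data and may lose precision

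*Protocol article*

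**What the plan says.** Two places in the Methods of the protocol article bear on this.

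- **Statistics and sample size.** The main test is stated as "We will thus use a single Wilcoxon-Mann-Whitney *U* (WMWU) rank sum test as our omnibus test". The difference is then explored by quantile regression at quantiles 0.1, 0.25, 0.5 and 0.75, "with DAOH_90_ as the outcome, and time, intervention and site as the predictors". No patient covariate is in that list. The stated power for this model is "77.7% power to detect an intervention effect using quantile regression (both two-tailed α < 0.05), with just over 10,000 patients", for "a 2 DAOH difference at quantile 0.25 between groups".
- **Outcome and patient-related data.** The variables to be collected are "age, gender, ethnicity, weight, height, surgical procedure (including primary or re-operation status) and known comorbidities", with emphasis on diabetes, severe renal disease, obesity and smoking. The rule for using them is: "Uncontrolled significant differences in rates of these covariates between groups will be statistically accounted for using quantile regression".

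The Primary outcome section adds a general promise to allow for confounders but names none. Nowhere is a covariate included because it is expected to predict the outcome.

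**The concern.** The two places together give a base model plus whatever covariates differ significantly between groups. That criterion asks the wrong question. What a covariate contributes to the intervention estimate depends on how strongly it predicts the outcome, as well as on imbalance. A significance test of imbalance sees only the second.

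Three things follow.

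1. A strong predictor that happens to balance is left out, and the precision it offers is given up.
2. The final model is settled only after the control and bundle cases have been compared.
3. In quantile regression the covariates define which conditional quantile is estimated. A set chosen from the data therefore makes the estimated quantity itself depend on the data, unless the effect is the same shift throughout the distribution.

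The intervention terms of these models are what the protocol says it will report, with their significance, to describe where any effect lies. The covariate rule therefore bears on the published effect sizes.

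**Working it through.** **The plan's own figure.** The 77.7% comes from the investigators' simulation on site-level distributions that the article does not show, so it cannot be recomputed. It is taken as given.

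**Step 1: what 77.7% implies.** At two-sided α = 0.05, effect/SE = z(0.975) + z(0.777) = 1.960 + 0.762 = 2.722.

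**Step 2: power if covariates remove a share v of the variance of the intervention estimate.** Power = Φ(2.722/√(1 − v) − 1.960). The share v is an assumption, because the document gives no association between covariates and outcome.

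| v | 2.722/√(1 − v) | Power |
|---|---|---|
| 0 | 2.722 | 77.7% |
| 2% | 2.750 | 78.5% |
| 5% | 2.793 | 79.8% |
| 10% | 2.869 | 81.8% |
| 20% | 3.043 | 86.1% |

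This is a mean-scale approximation applied to a quantile model, and it holds the effect at the value behind the 77.7%.

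**Step 3: does the gain carry over to quantile 0.25?** A simulation used five equal sites, six periods, about 10,984 cases, an assumed log-normal length of stay and three prognostic covariates balanced across sites. It compared the variance of the intervention estimate with and without the covariates.

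- Covariates explaining 24% of within-site variance: ratio 0.59.
- Covariates explaining 11%: ratios 0.78 and 0.80 in two runs.
- Covariates explaining 3%: ratios 1.10 and 0.88, so no clear gain.

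**Step 4: what the trigger selects.** A 5% test on a covariate that is balanced apart from chance leaves it out about 95% of the time, however prognostic it is.

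Elsewhere in the article a group is all control or all bundle cases ("we will recruit 5492 cases in each group"). If the trigger is a pooled test of that kind, it also responds to site mix. With equal caseloads (assumption), the first site to cross over supplies 1 of 15 control site-periods and 5 of 15 bundle site-periods, and the last site the reverse. The differences in site weight are −4/15, −2/15, 0, 2/15 and 4/15 in size, and their squares sum to 40/225 = 0.178. For a covariate with intracluster correlation ρ and unit variance:

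- variance from site mix = 0.178ρ
- sampling variance ≈ 2/5492 = 0.00036
- at ρ = 0.02, the SD of the test statistic is about 3.3, so P(|Z| > 1.96) ≈ 55%
- at ρ = 0.005, about 29%
- at ρ = 0.001, about 11%

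A simulated 20% binary covariate unrelated to treatment was selected in 4%, 13%, 45% and 68% of runs when site prevalence varied by 0, ±2, ±5 and ±10 points. A test adjusted for site and period selected it in about 4% to 7%.

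**The case against.** **The site-mix argument is easily overstated.** A reader might infer that about half the covariates would enter through site mix alone and that this distorts the result. The document does not support that, for three reasons.

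- The sentence says neither *only* nor *pooled*, and it begins with *uncontrolled*. That word can mean differences not already handled by the time and site terms. On that reading selection follows chance or within-site drift, and the site-mix rates above do not apply.
- Site is already a predictor, so between-site imbalance in covariates is largely absorbed. Covariates picked up through site mix do little harm, and including them moves towards the fuller model recommended here.
- The 55% borrows an intracluster correlation ("The intracluster correlation coefficient was measured as 0.02") that the article does not report for any covariate.

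All of this stands.

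**The main analysis is elsewhere.** The omnibus rank sum test has no stated covariate adjustment and is untouched. The rule is also stated in advance and looks at covariates rather than outcomes, so it does not by itself let anyone choose a favourable result. Both points stand, and they limit the concern to the quantile regression.

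**The gain may be small.** The clusters include a cardiac unit and a children's hospital, so site already carries part of the information in age and procedure. The simulated covariates were balanced across sites, which favours adjustment. This stands too.

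**The covariate list belongs in an analysis plan.** This is true of a full list. But the article does not leave the matter open: it states a significance trigger. The trigger is the point at issue, and on either reading of *uncontrolled* it ignores prognosis.

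**Conclusion.** The point holds as an improvement to the quantile regression. The stated trigger for covariate adjustment disregards prognosis and makes the adjusted model, and the quantile it estimates, depend on observed group comparisons. The likely cost is precision in the analysis whose stated power is 77.7%.

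The size of that cost is unknown. Power of about 78.5% to 86.1% corresponds to an assumed 2% to 20% reduction in the variance of the intervention estimate, and the gain could be close to nil if covariates add little beyond site.

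No bias has been shown, either in the rank sum test or in the time-intervention-site model. The site-mix behaviour of a pooled test is a further reason not to use significance as the criterion, but it is not itself a source of material error, since site is in the model.

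**What to change.** Replace the significance trigger with a covariate set named in advance from the data already being collected. An example is age, sex, ethnicity, procedure type, primary or re-operation status, diabetes and severe renal disease, with obesity and smoking where they are meaningful given the children's cluster. Include that set with site and time in every quantile model, whatever the observed balance, and drop significance tests of covariates between groups. Keep the time-intervention-site model as a sensitivity analysis, and say that the 77.7% refers to that model.

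The wording change is about a sentence in the protocol or analysis plan, and no new data are needed. There are two small costs. Rules must be set for missing weight, height and smoking. If a power figure is wanted for the adjusted model, the simulation must be rerun, because the approximation above does not replace it.

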#### Adverse events and Data and Safety Monitoring Committee

Patients often experience adverse events related to surgery and anaesthesia, and recording and reviewing these events will not be practicable in this study. Any adverse event related or possibly related to the bundle that occurs before the patient leaves the post-anaesthesia area will be recorded on an Adverse Events Form. The primary investigators will be notified of any serious adverse events attributable to the study in writing within 24 h of becoming aware of such an event taking place.

Each adverse event related to the bundle will be classified by the primary investigators as:Non-filter-related adverse eventFilter-related adverse event

Each filter-related adverse event will be assigned a severity classification as follows:*Mild*. Events cause awareness of signs or symptoms but are easily tolerated and are of minor irritant type, causing no loss of time from normal activities. Symptoms do not require therapy or a medical evaluation; signs and symptoms are transient.*Moderate*. Events introduce a low level of inconvenience or concern to the patient and may interfere with daily activities but are usually improved by simple therapeutic measures; moderate experiences may cause some interference with functioning.*Serious*. Events interrupt the patient’s normal daily activities and generally require systemic drug therapy or other treatment; they are usually incapacitating.

A Data and Safety Monitoring Committee will be formed and will be responsible for reviewing such serious adverse events as they arise.

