We note that the study is not powered to show a difference in our secondary outcome, surgical site infection. Reducing surgical site infections from a base rate of about 1.4% (a reasonable estimate of the overall rate at present) to 0.8% would require approximately 11,000 patients (5500 in each group, one-tailed α = 0.05 and β > 0.8: estimated with MedCalc [MedCalc Software, Ostend, Belgium]). If we allow for cluster allocation by assuming a design effect of 2.0 (intracluster correlation coefficient = 0.02), the required number is likely to be double this. Given the likely proportion of Māori and Pacific patients, it is also not powered to investigate differences between these patients and other subgroups in the study, and any analysis of such differences will be exploratory and hypothesis-generating in nature.

An interim analysis will be performed after 12 months of data collection (i.e. at the end of Step 2, Table 2) to verify the safety of the intervention as indicated by an absence of serious adverse events related to the bundle. We will also verify the completeness of the study data. In addition, an independent monitor will be employed to verify that the study processes do protect the rights of the participants; the reported study data are accurate, complete and verifiable from source documents; and the conduct of the study is in compliance with approved protocol/amendment(s), with Good Clinical Practice and with the applicable regulatory requirements.

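### Serious is defined as the top grade of an intensity scale, is assigned only to filter-related events, and is tied to causality thresholds that differ between form, 24-hour notice and interim analysis

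*Protocol article*

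**What the plan says.** Safety reporting is set out in the section on adverse events and the Data and Safety Monitoring Committee. General adverse events of surgery and anaesthesia are not collected. What is collected is limited by cause and by time: "Any adverse event related or possibly related to the bundle that occurs before the patient leaves the post-anaesthesia area will be recorded".

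The next step is a split into filter-related and non-filter-related: "Each adverse event related to the bundle will be classified by the primary investigators". Only one branch is then graded: "Each filter-related adverse event will be assigned a severity classification as follows". The grades are mild (in part, "causing no loss of time from normal activities"), moderate (in part, "may interfere with daily activities but are usually improved by simple therapeutic measures") and serious: "Events interrupt the patient’s normal daily activities and generally require systemic drug therapy or other treatment; they are usually incapacitating". The article gives no other definition of a serious adverse event.

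Three later steps depend on that word. The primary investigators "will be notified of any serious adverse events attributable to the study in writing within 24 h". The committee reviews such serious events as they arise. Under Statistics and sample size, the interim analysis after 12 months is to verify safety "as indicated by an absence of serious adverse events related to the bundle".

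**The concern.** Seriousness (what the event led to) and intensity (how strongly it was felt or how much it interfered) are normally two separate judgements. Here they are one scale, worded for people going about everyday life. The events to be graded arise during anaesthesia, sedation or immediate recovery, and one of the five clusters is at a children's hospital. Different graders could reasonably place the same event differently.

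The word also has several functions. It decides what is notified urgently, what the committee sees, and what the interim analysis reports as its stated indicator of safety. If it is loosely defined, applied to only part of the intervention, and combined with a causality test that changes from step to step, those three steps may not be looking at the same set of events. This matters more than usual here because patients do not give individual consent, approval rests partly on the intervention being low risk, and this is the only adverse-event reporting route the article describes.

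**Working it through.** No arithmetic applies: the safety section states no rate or count. The check sets the stated rules side by side.

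**Content of the three grades (paraphrased)**

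| Grade | Everyday activities | Treatment | Other |
|---|---|---|---|
| Mild | no time lost | no therapy or evaluation needed | patient is aware of signs or symptoms; transient |
| Moderate | may be affected | simple measures usually help | some inconvenience or concern |
| Serious | interrupted | systemic drug or other treatment, generally | usually incapacitating |

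1. All three grades refer to everyday activities. While the patient is still in the recording window, no such activities are under way and incapacity is the expected state, so the grader must judge what the event would cause, or later did cause. The article does not say which, when, or who assigns the grade.
2. The treatment descriptor does not fix the boundary. A single drug dose can be both a systemic drug treatment (serious) and a simple measure (moderate), and the descriptor is softened by the word generally.
3. Mild relies on the patient being aware of signs or symptoms, which an anaesthetised patient is not and a small child may not be able to report.
4. Death, threat to life, prolonged stay and lasting harm appear in none of the grades.

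**Scope and causality at each step**

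| Step | Needs the word serious? | Events covered | Causality wording |
|---|---|---|---|
| Adverse Events Form | no | whole bundle | related or possibly related |
| Filter / non-filter split | no | whole bundle | related |
| Severity grade | assigns it | filter-related only | follows from the split |
| 24-hour notice | yes | the study | attributable |
| Committee review | yes | refers back to such serious events | not restated |
| Interim criterion | yes | whole bundle | related |

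**Tracing two hypothetical events through these rules**

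- *A severe reaction to a non-filter element*, such as the skin wipe. It goes on the form and is classified as non-filter-related. No grade is assigned. The interim criterion nevertheless counts serious events related to the bundle, so someone must decide whether it is serious without a rule.
- *A filter-related event graded serious but judged only possibly related to the bundle.* It goes on the form. The 24-hour notice applies to events attributable to the study. Unless attributable is read to include possibly related, which the article does not say, urgent notice is not required. The interim wording, related, leaves the same doubt.

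Both gaps follow from applying the printed rules as they stand. Neither depends on how the intensity scale is interpreted.

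**The case against.** Several objections limit the point.

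- *Timing of the judgement.* The article restricts when an event occurs, not when its effect is judged. A patient who is unconscious from anaesthesia has not been incapacitated by the event. A reader might infer that the descriptors can never tell events apart in this setting; the text does not support that, because effects can be assessed after recovery. What stands is that the wording is awkward and open to different readings.
- *Grave events.* A reader might infer that the safety trigger fails altogether. It does not: a catastrophic event would probably still be graded serious through the reference to systemic drug or other treatment. The uncertainty lies mainly at the boundary with moderate and for events outside the filter branch.
- *Possibly related events are not lost.* They are still recorded on the form. What is limited is urgent notice. The article also sets no standard for attributable, so a generous reading could include them, but that reading is not written down.
- *Consequences of one event.* A reader might infer that a single misgraded event would overturn the trial's safety conclusion. The article attaches no automatic action to one event; its Early termination section makes stopping a judgement based on the nature of the event, certainty of association and likelihood of recurrence.
- *Other sources.* Death and hospital days to 90 days are captured through the primary outcome, though without attribution to the bundle, so this does not replace event reporting.
- *Condensed article.* The full protocol (version 1.3) and the Adverse Events Form are not shown and may say more. That would excuse silence. Here the article itself prints a definition, a scope and three causality wordings, and these do not agree.

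**Conclusion.** The point holds as a definition and consistency problem that should be corrected. It has three parts: an intensity grade serves as the definition of seriousness, with a loose boundary to moderate and no outcome criterion; the grade is confined to filter-related events while the interim criterion covers the whole bundle; and causality is worded differently for the form, the 24-hour notice and the interim analysis.

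The last two are the firmer parts, because the printed rules leave non-filter events ungraded and possibly related serious events outside the 24-hour notice. The first part makes grading hard to apply consistently.

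The size cannot be put in numbers: the article gives no expected rate of bundle-related events, and its authors expect no complications. The effect is on the reliability of urgent notice, committee review and the interim safety statement, not on the primary analysis. The conclusion assumes that the fuller protocol and the form repeat the article's rules; if they already reconcile them, only the article's wording is at fault.

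**What to change.** 1. Give one outcome-based definition of a serious event (covering, for example, death, threat to life, prolonged stay and lasting harm), and apply it to all bundle-related events, filter and non-filter alike. The exact list is for the investigators and the committee to settle.
2. Keep mild, moderate and a renamed top grade as a separate intensity scale, with wording usable for events arising under anaesthesia and in children. State who assigns it and when.
3. Reconcile the causality threshold across the form, the 24-hour notice, committee review and the interim analysis, using the related-or-possibly-related threshold the form already applies.

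The cost is one protocol paragraph and an edit to the form. The downside is a few more 24-hour reports. No sample size or outcome analysis changes.
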